##### Tendon thickness

All parameters are measured on the left side of the Achilles tendon and then the right side of the Achilles tendon. Greyscale ultrasound is used initially to identify the Achilles tendon. Longitudinal scans are performed medially and laterally across the Achilles tendon until the scan plane shows the Achilles tendon clearly, and maximum tendon thickness is obtained. To minimise the anisotropic effect, the transducer is adjusted so that the ultrasound beam is perpendicular to the tendon fibres. A greyscale sonographic image is taken of the Achilles tendon. Tendon thickness is measured with grayscale and axial ultrasound at the region of interest [12].

##### Neovascularity

The transducer is placed perpendicular to obtain a sagittal view of the Achilles tendon at the most painful part on palpation. The upper limit of the colour box is set on the dorsal side of the tendon. Pressure from the transducer is kept to a minimum to prevent the occlusion of neovascularization. The assessor screens the tendon for the area of maximum Doppler flow during the preparation phase for 1 min. The transducer is gently moved to medial and lateral over where Doppler flow is present. When the location of the maximum Doppler flow is identified, a sonographic image is taken. The modified Öhberg score from 0 to 4 + is determined during the US examination. In this scoring system, scores are determined as 0 (no vessels), 1 + (1 vessel, primarily anterior to the tendon), 2 + (1 or 2 vessels throughout the tendon), 3 + (3 vessels throughout the tendon), or 4 + (more than three vessels throughout the tendon). A higher score indicates more Doppler flow in the peritendinous and intratendinous tissues [13].

##### Tendon elasticity

Shear wave elastography (SWE) quantifies soft tissue stiffness and provides an absolute value of tendon stiffness [12]. Once the optimal scan plane of the tendon is identified, the SWE function is activated. SWE is set at the penetration mode with the measurable range of stiffness standardised at 0–600 kPa. The SWE colour map (height × width: 1.4 cm × 1.3 cm) is placed just above the superior border of the calcaneum. Electrogram is obtained and stored when the colour signals become steady for five seconds. Tendon stiffness is measured with the stiffness measurement tool—Q-box. The circular measurement area (Q-box) is set to 2 mm in diameter, dependent on the tendon size, and covers the Achilles tendon without including other adjacent soft tissues. Q-box is placed at the middle part of the tendon within the SWE colour map. For each Q-box, the mean (in kPa) of the stiffness of the tendon is measured [14].

The ultrasound normalisation procedure for subjects with bilateral tendinopathy will be done by using the mean values measured in healthy individuals as stated in current evidence. The mean value of a healthy Achilles tendon was reported to be 5.3 mm [15]. No vessels appear throughout the Achilles tendon for a healthy tendon (Öhberg score 0) [16]. The range of tendon elasticity measured in shear wave elastography in men and women are 657.1–766.4667 kPa and 433.5677–782.8667 kPa, respectively [17].

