**Inclusion criteria**
(1) Age between 18 and 70 (2) Focal clinical signs of AT with localised tenderness on palpation of the Achilles tendon (3) Recurrent complaints in 1 or both Achilles’ tendons at rest and during exercise for the preceding 3 months (4) Structural changes of the tendon were confirmed via sonographic examination during the initial physical exam (5) Informed consent

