## Discussion

AT is a clinical syndrome characterised by pain, swelling, and functional impairment, indicating a degenerative inflammatory process in the Achilles tendon. The overall incidence rate of AT was 2.45 per 1000 in the adult population between 21 and 60 years in their lifetime. It can affect athletes and non-athletes. Patients with AT commonly refer to persistent pain that may result in loss of function and activity cessation. The pathogenesis of tendinopathy can be described as failed healing of the diseased tendon. Failed recovery mainly refers to prolonged inflammation and failed resolution of the normal healing process. Furthermore, increased focal vascularity contributes to the clinical presentations of chronic tendon pain, stiffness, and weakness.

An increase in tendon thickness is often found in patients with AT. It could happen in either midportion or insertion of the Achilles tendon, which is caused by swelling of the affected area. Moreover, the ingrowth of new blood vessels into tendinopathic regions is often seen in ultrasound imaging. PEMF may reduce tendon inflammation, thus reducing tendon thickness and neovascularity. Tendon elasticity is measured by shear wave elastography (SWE). SWE could quantify soft tissue stiffness and provide an absolute value of the stiffness of the soft tissue. There may be an increase in tendon stiffness in patients with AT. This is because patients may reduce the level of activities because of pain associated with AT. PEMF may minimise tendon pain and facilitate the performance of the eccentric exercise. Thus, there may be a reduction in tendon elasticity.

This trial may demonstrate the effectiveness of PEMF in relieving pain, improving function, and restoring mechanical changes of the tendon in patients with AT. AT is a common clinical condition affecting both athletes and sedentary populations. Exercise prescription is used as a non-invasive therapy for patients with AT. However, some participants do not respond well to exercise therapy and conventional treatments. It is essential to investigate treatment adjuncts to improve rehabilitation outcomes for this group of patients.

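### Shear-wave stiffness is limited to 600 kPa, below the whole male and about half the width of the female reference range that the protocol cites for the same outcome

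*Protocol article*

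**What the plan says.** All of the main text is in the protocol article, section Tendon elasticity. The device setting is given as: "SWE is set at the penetration mode with the measurable range of stiffness standardised at 0–600 kPa". The recorded quantity is the mean stiffness in kPa within a circular measurement area (Q-box) of 2 mm diameter, and the section describes the method as giving an absolute stiffness value.

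The next paragraph turns to normalisation: "The ultrasound normalisation procedure for subjects with bilateral tendinopathy will be done by using the mean values measured in healthy individuals". It then supplies the references. Thickness gets one value, 5.3 mm. Neovascularity gets an Öhberg score of 0 ("No vessels appear throughout the Achilles tendon for a healthy tendon"). Elasticity gets two ranges: "The range of tendon elasticity measured in shear wave elastography in men and women are 657.1–766.4667 kPa and 433.5677–782.8667 kPa, respectively".

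Bilateral cases are eligible, since Table 1 admits "Recurrent complaints in 1 or both" Achilles tendons. On direction, the Discussion says: "There may be an increase in tendon stiffness in patients with AT", and suggests that treatment may lower it. The article does not say how a reading at the upper limit is to be handled.

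**The concern.** Two figures for the same outcome, one paragraph apart, do not fit together. A setting whose measurable range stops at 600 kPa cannot return a value inside the male reference range, and cannot return one in roughly the upper half of the female range. Yet those ranges are the yardstick for bilateral cases.

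Readings of stiff tendons would then collect at the limit. The same limit applies in both arms, so the expected effect is to shrink a real difference between PEMF and sham, not to create a false one. The second objective of the trial covers the mechanical and morphological properties of the tendon, and elastography is scheduled at every assessment. With 40 participants, a diluted result could be read as evidence that PEMF does not change tendon mechanics. No later analysis can recover stiffness that the device did not record.

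A second, smaller gap is that the text promises mean values as references but gives no mean for elasticity. A bilateral participant therefore has no single defined reference.

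**Working it through.** The plan gives no computed figure for this point, so the check compares its stated numbers and then illustrates the consequence.

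**Inputs from the section Tendon elasticity.** Upper limit 600 kPa; men 657.1–766.4667 kPa; women 433.5677–782.8667 kPa. The sentence with the ranges does not repeat the word healthy. Its place in the paragraph on healthy references makes that the natural reading.

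**Step 1: position of the limit.** Share of the range width above the limit = (upper − 600)/(upper − lower), bounded to 0–1.

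- Men: the lower end exceeds the limit by 657.1 − 600 = 57.1 kPa and the upper end by 766.4667 − 600 = 166.5 kPa. The share is 100%.
- Women: (782.8667 − 600)/(782.8667 − 433.5677) = 182.8667/349.299 = 0.524. The midpoint, (433.5677 + 782.8667)/2 = 608.2 kPa, is also just above the limit.

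These are shares of an interval. The article gives no distribution within it, so they do not estimate how many people or scans would reach 600 kPa.

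**Step 2: what a limit does to a treatment difference.** Assumptions, not in the document: individual stiffness X is normal with SD s = 100 kPa, treatment lowers the mean m by 50 kPa, and any value above 600 is read as 600. The mean reading is

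E[min(X, 600)] = mΦ(a) − sφ(a) + 600(1 − Φ(a)), with a = (600 − m)/s.

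Example for m = 600: the mean reading is 600 − 100 × 0.3989 = 560.1. For m = 550 it is 550 × 0.6915 − 100 × 0.3521 + 600 × 0.3085 = 530.2. The visible shift is 29.9 of 50 kPa, or 60%.

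| Mean without the shift (kPa) | Share of people above 600 | Share of the 50 kPa shift still visible |
|---|---|---|
| 300 | 0.1% | 99.9% |
| 400 | 2.3% | 99% |
| 500 | 15.9% | 89% |
| 600 | 50% | 60% |
| 700 | 84.1% | 23% |

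The result depends almost wholly on where the participants lie, which the document does not say. Its own references point to the lower rows for men and to about the fourth row for women (midpoint 608.2).

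**Step 3: reference values.** Thickness and Öhberg score each have one number. Elasticity has two sex-specific ranges and no mean, so the promised reference is not fixed. Any value taken from the male range exceeds everything that the trial's setting can record.

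**The case against.** The strongest reply is that the conflict may have little consequence. No section reports participants' stiffness. If it averages about 400 kPa or less, almost nothing is lost. The cited ranges may also come from another device mode or ankle position than the relaxed prone scan used here, and the source is not at hand. This stands as far as the size of the effect goes. It does not rescue the plan, because references from a different set-up would be unsuitable for normalising this trial's scans.

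It might also be said that 600 kPa is only a display scale. The article calls it the measurable range. If it is only a display scale, the text should say so.

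Several stronger readings are tempting, and the document does not carry them:

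- A reader might infer that elasticity is censored as a matter of fact. Only the mismatch is documented.
- A reader might take the Discussion to place diseased tendons above the cited ranges. It says only that stiffness may be increased, and compares nothing with those figures.
- A reader might compute that a bilateral man can reach at most 600/766.4667 = 78% to 600/657.1 = 91% of healthy, or that an Öhberg reference of 0 makes the normalised score undefined. Both assume division. The formula is not stated, and a difference from 0 is well defined.
- A reader might conclude that unilateral cases must sit on another scale, such as the opposite leg. Their normalisation is not described, and the statistical methods section does not say that normalised values are what is analysed. Such details may properly sit in an analysis plan that is not shown.

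**Conclusion.** The concern holds in a limited form. The measurable range and the reference values contradict each other, and nothing else in the article resolves this. For men the gap is complete (57.1 to 166.5 kPa above the limit). For women it covers 52% of the range width. Whatever the normalisation formula, the bilateral reference for men lies on a scale that the trial's setting cannot record, and the promised mean for elasticity is missing.

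The consequence is conditional. Under the assumed SD of 100 kPa and shift of -50 kPa, the dilution runs from about 1% at a mean of 400 kPa to 40% at 600 and 77% at 700. Confidence is high for the mismatch and much lower for its effect. It concerns a secondary outcome and mainly weakens a difference; the VISA-A analysis is untouched. It should be corrected, but it does not threaten the trial's main conclusion.

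**What to change.** 1. Reconcile the measurable range with the cited references in the section Tendon elasticity, and say whether 600 kPa limits measurement or only display.
2. For participants not yet scanned, use a range that covers the cited maximum (782.8667, so 783 kPa) if the device allows. Keep one setting throughout each participant's visits. Enrolment began in July 2021, so a change partway through a participant's follow-up would mix settings within that person.
3. For scans taken at 0–600 kPa, flag every Q-box that reaches the limit and analyse it as right-censored. Include partial saturation: the outcome is a mean over the Q-box, so a mean below 600 may already contain capped values, which a simple Tobit limit at 600 on the mean would miss.
4. Analyse raw stiffness (kPa), thickness (mm) and Öhberg grade of the treated tendon, adjusted for its baseline value, instead of values normalised to published constants in bilateral cases. The missing elasticity mean then no longer matters. If normalisation is kept, state one elasticity reference value per sex.

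Cost: revised measurement and analysis wording, a review of stored scans for saturation, a censored-data analysis for existing scans and, if the setting is changed, an indicator for device setting in the model. The changed setting also leaves some difference in comparability between earlier and later participants, which the indicator only partly addresses.

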### Participant timeline {13}

Table 2 is used to demonstrate the schedule of enrolment, interventions, assessments, and visits for participants.

**Table 2 Tab2:** Participant timeline

	Study period						
	Enrolment	Allocation	Post-allocation				
Timepoint	Before allocation	0	Week 1	Week 4	Week 8	3 months	6 months
Enrolment:							
Eligibility screen	X						
Informed consent	X						
Allocation		X					
Interventions:							
Control group: Sham PEMF plus eccentric exercise			X	X	X		
Experimental group: Active PEMF plus eccentric exercise			X	X	X		
Assessments:							
Self-reported questionnaires (NPRS, VISA-A, SF-36)			X	X	X	X	X
Functional outcomes (AROM, heel-rise)			X	X	X	X	X
Ultrasonographic outcomes (Tendon thickness, neovascularity, tendon elasticity)			X	X	X	X	X

*AROM* Ankle range of motion, *NPRS* Numeric pain rating scale, *SF-36* Short-form 36, *VISA-A* Victorian Institute of Sports Assessment-Achilles

### Sample size {14}

A minimum clinically significant difference is 16 points on the VISA-A scores based on the pilot study using VISA-A as the primary outcome in treating AT [18]. It was reported in a feasibility study using another conservative treatment, laser therapy as an adjunct treatment to eccentric exercise therapy for AT. A total of 20 participants were recruited and VISA-A was the primary outcome. Significant improvements were shown in both treatment groups in VISA-A [18]. The power calculation to detect the minimum clinically significant difference is conducted using the G Power programme at a type I error of 5%, power of 80% (correlation value, 0.03; pooled SD, 20.25). Twenty subjects per group are obtained to detect a significant difference in VISA-A among two groups if a two-way repeated-measures analysis of variance (ANOVA) is proposed. It is expected to have a 20% dropout rate. Thus, the final study sample size is 40 subjects in total [19].

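### The 40 participants include no allowance for the expected 20% dropout, and 20 per group does not follow from the stated inputs, so the 80% power claim is unsupported

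*Protocol article*

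**What the plan says.** All of this stands in the protocol article, Sample size {14}.

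- Target: "A minimum clinically significant difference is 16 points on the VISA-A scores", taken from a feasibility study of laser therapy added to eccentric exercise.
- Inputs: "at a type I error of 5%, power of 80% (correlation value, 0.03; pooled SD, 20.25". The calculation holds "if a two-way repeated-measures analysis of variance (ANOVA) is proposed".
- Result: "Twenty subjects per group are obtained to detect a significant difference in VISA-A among two groups".
- Dropout and final size: "It is expected to have a 20% dropout rate. Thus, the final study sample size is 40 subjects in total".

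Trial design {8} also randomises 20 and 20. The section does not say which ANOVA effect was powered or how many measurements were entered. Statistical methods {20a} plans a repeated-measures two-way ANOVA over five assessments: baseline, 4 weeks, 8 weeks, 3 months and 6 months. Section {20c} plans intention-to-treat analysis with multiple imputation under missing at random.

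**The concern.** Two things do not fit. First, the final number is presented as the consequence of the dropout rate, yet it equals the number before dropout. Second, the paragraph prints enough inputs to be checked, and 20 per group does not come out of them.

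The correlation also deserves attention. A value of 0.03 treats repeated VISA-A scores from one patient as almost independent. That makes a group effect averaged over several visits look very precise, and no justification is given.

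At stake is how a null result on the primary outcome will be read. With 80% power for the trial's own minimum important difference, a non-significant result says something about that difference. If the true figure is unknown, or lower, that reading is not available.

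**Working it through.** **Inputs.** From {14}: difference 16, SD 20.25, correlation ρ = 0.03, α = 5%, power 80%, dropout 20%. An ANOVA F test has no direction, so 5% is taken as two-sided. From {20a}: five measurements. Not stated: the effect powered and the number of measurements used, so 2 to 5 are tried.

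**Step 1: dropout.**
- Stated requirement: 2 × 20 = 40. Stated final size: 40. Added: 0.
- Inflated requirement: 20/(1 − 0.20) = 25 per group, 50 in total.
- Reverse reading: 40 × 0.80 = 32, or 16 per group, which contradicts the stated 20.
- If 20 per group gave exactly 80%, power with 16 is Φ(2.80 × √(16/20) − 1.96) = Φ(0.546) ≈ 0.71; with the noncentral t it is 0.70.

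**Step 2: reproducing 20 per group.** Standardised difference 16/20.25 = 0.790; Cohen's f = 0.790/2 = 0.395.

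*One visit, unadjusted.* n = 2(1.960 + 0.842)²/0.790² = 25.1, so 26 per group by the normal formula and 27 by the t test. Power is 68% with 20 per group and 58% with 16. The difference detectable with 80% power is 18.4 and 20.7 points.

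*Repeated-measures ANOVA, m measurements, N in total (noncentral F).*
- Group effect: λ = f²Nm/[1 + (m − 1)ρ], df 1 and N − 2.
- Interaction: λ = f²Nm/(1 − ρ), df m − 1 and (N − 2)(m − 1).
- The generic interaction uses f = 0.395. With no difference at baseline and 16 points at every later visit, the interaction f is 0.395 × √(m − 1)/m, which is 0.198, 0.186, 0.171 and 0.158 for m = 2 to 5.

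Total N for 80% power at ρ = 0.03:

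| Effect | m = 2 | m = 3 | m = 4 | m = 5 |
|---|---|---|---|---|
| Group, f = 0.395 | 28 | 20 | 16 | 14 |
| Interaction, generic f = 0.395 | 28 | 22 | 20 | 18 |
| Interaction, no baseline difference | 100 | 92 | 92 | 94 |

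No cell is 40, and none is 32, the figure that would become 40 after a 20% allowance.

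*Routes that do reach 20 per group* each need an input that {14} does not give: a one-sided normal formula, 2(1.645 + 0.842)²/0.790² = 19.8; a correlation of 0.5 with two measurements (40 in total for the group effect) or in a baseline-adjusted comparison (20 per group); or a generic f of 0.25 for a five-measurement interaction.

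**Step 3: how far the answer depends on the effect and the correlation.** For the five-visit group effect with no baseline difference, the average difference is 16 × 4/5 = 12.8, so f = 12.8/(2 × 20.25) = 0.316. For N = 40, λ = 0.316² × 40 × 5/(1 + 4ρ), which is 17.8 at ρ = 0.03 and 6.66 at ρ = 0.5. For N = 32 it is 14.3 and 5.33.

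| Test, 16 points after baseline | Power, 40 analysed | Power, 32 analysed |
|---|---|---|
| Five-visit group effect, ρ = 0.03 | 98% | 95% |
| Five-visit group effect, ρ = 0.5 (assumed) | 71% | 61% |
| Five-visit interaction, ρ = 0.03 | 40% | 32% |
| Five-visit interaction, ρ = 0.5 (assumed) | 70% | 58% |
| One visit, unadjusted | 68% | 58% |

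A higher correlation lowers the power of the group effect and raises that of the interaction, so no single value is conservative for both.

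**The case against.** The strongest objection is that a reader might infer from Step 1 and the one-visit figures that the trial is simply underpowered, well short of 80%. The documents do not support that as a general statement. Taken literally, the stated test and inputs give more than 80% with 32 analysed: 85% to 99.5% for the group effect with f = 0.395, 87% to 99% for the generic interaction, and 95% for the five-visit group effect with no baseline difference. The 68% and 58% belong to an unadjusted one-visit test, which is not the test named in {14}. The 71% and 61% rest on a correlation of 0.5 that the protocol does not state. This part of the objection stands, and the point is limited accordingly.

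A second objection concerns missing data. Section {20c} plans multiple imputation, and participants who leave may already have contributed early scores. Power with 32 complete cases is therefore a pessimistic bound. That also stands, but imputation does not restore all the lost information, and it does not turn 40 into a number that contains an allowance.

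Third, the size, allocation and analysis would not change, and a null result can be read from its confidence interval. True, but the 80% figure is still a printed planning claim for the primary outcome, and the paragraph does not support it.

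That the article condenses a longer protocol does not help: inputs, result, dropout rate and conclusion are all printed, and the fault is in what they say.

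**Conclusion.** The dropout part is firm and needs no assumption: the number before and after the allowance is the same, so either no allowance was made or the 20 per group is not the calculated requirement. If 20 per group did give 80%, the expected loss would bring it to about 70%, treating dropouts as contributing no data.

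The non-reproduction is also firm for the stated test, SD, difference and correlation, over 2 to 5 measurements and the effects tried. Because unstated inputs can produce 20 per group, the figure is unsupported rather than proven a slip of calculation.

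The direction of the error is not established. With 32 analysed, power for 16 points runs from 32% (five-visit interaction, no baseline difference, correlation 0.03) to above 95% (group effect over several visits at the same correlation). Likewise, 50 in total should not be read as the correct size: it only inflates a figure of 20 that itself has no support.

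**What to change.** Keep 40 and rewrite the paragraph in {14}:

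1. State 40 randomised and about 32 expected completers at 20% dropout, and delete the *Thus* that presents 40 as containing a dropout allowance.
2. Say which effect of the planned repeated-measures ANOVA is the primary test, group or group-by-time, with the number of measurements and the assumed pattern of differences, including zero at baseline.
3. For that effect, give the power for 16 points and the difference detectable with 80% power, at 40 and at 32 analysed.
4. Replace the single correlation of 0.03 with a justified range, for example 0.3 to 0.7, marked as an assumption.

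The cost is wording and a short recalculation. No extra participants are needed, and enrolment, which began in July 2021, is unaffected. The stated power may become less favourable.
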